### 2.5. Randomization and Blinding

A member of the Good Clinical Practice (GCP) Clinical Center of Xiyuan Hospital who is independent of the study will use SAS 9.2 software to perform a block randomization, generating a sequence of 72 random numbers in 1 : 1 allocation between the two groups. In order to conceal the generation, the outcomes will be conducted by another member of GCP Clinical Center using a central randomization; once a patient meets all the criteria, a random number will then be delivered by telephone to the clinical researchers, unblinding only after data is collected for the first phase of the study (see Section 2.9). The number delivered by telephone will determine whether the subject receives the control or experimental therapy. 

Because the color of the STS solution given to the experimental group is unique and challenging to emulate, blinding will be difficult to achieve at the physician and patient levels. In order to minimize biases as much as possible, all other potential sources of information that may reveal treatment allocation to patients (e.g., contents of case report form, patient's random number) will be judiciously guarded. Additionally, the details of treatment allocation will not be disclosed to any patient until the study has concluded, and all study participants will be discouraged from discussing with one another their involvement in the trial. Finally, the clinical researchers will strictly abide by the study's random design and will interact with the patients in each group with as few differences as possible.

Blinding will be maintained at the level of outcome assessment. The individuals performing laboratory blood analyses, data management, and statistical analyses will be independent of the clinical component of the study and will not be provided with any information that may reveal treatment allocation details. 

### 2.6. Ethics

This trial has been approved by the local institutional ethics committee (Xiyuan Hospital, China Academy of Chinese Medical Sciences, Beijing, China; (2012XL022-2)) and is registered at the Chinese Clinical Trial Registry (ChiCTR-TRC-12002361). All aspects of our study will be conducted with adherence to the current version of the Declaration of Helsinki, the guidelines established by the International Conference on Harmonization of Good Clinical Practice, and the laws of China. Informed written consent will be required of all study participants, none of whom will be denied a standard, accepted therapy. 

### 2.7. Treatment

Each patient in the standard Western therapy (control) group will receive 20 mg simvastatin orally once per evening, in addition to any other oral or IV Western medications or TCM preparations (aside from those listed as exclusion criteria, above) that are deemed appropriate for a standard treatment of the patient's individual condition. These other medications will be prescribed by physicians who are not associated with the trial.

In addition to receiving the treatments described above for the control group, each patient in the East-West integrative therapy (experimental) group will also receive a daily intravenous dose of 80 mg STS (10 mg per ampoule, Jiangsu Carefree Pharmaceutical Co., Ltd., national drug approval number: H31022558), diluted with 250 mL 0.9% NaCl solution.

All study participants will receive treatment as indicated above for 14 consecutive days. 

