The danshen root contains tanshinone IIA, an active biochemical compound that has been shown to possess a multitude of antiatherosclerotic properties [8]. Most noteworthy is the ability of tanshinone IIA to decrease the levels of numerous inflammatory mediators associated with the progression of atherosclerosis, such as CRP, interleukin-6 (IL-6), tumor necrosis factor alpha (TNF*α*), vascular cell adhesion molecule-1 (VCAM-1), CD40, monocyte chemotactic protein-1 (MCP-1), and matrix metalloproteinase-9 (MMP-9) [8, 9]. A recent clinical trial demonstrated that giving simvastatin in combination with intravenous sodium tanshinone IIA sulfate (STS), the most widely used clinical formulation of tanshinone IIA in China, significantly decreased the levels of CRP, cholesterol, and plaque buildup in patients with peripheral vascular disease [10]. Notably, the integrative therapy was safer and more effective in treating this form of atherosclerosis than simvastatin alone. Whether there is potential for synergy between STS and statins in treating CHD, however, remains unknown.

Here, we present the protocol for a randomized, controlled clinical study that applies East-West integrative medicine to the treatment of CHD. Using standard Western therapy involving simvastatin as a foundation, we aim to explore the potential of further dampening the atherosclerotic inflammatory reaction in CHD-BSS patients through the concomitant addition of STS, utilizing the compound's potent anti-inflammatory properties as a supplement to simvastatin. In addition, we also aim to assess the integrative therapy's safety and its efficacy in improving angina and BSS symptoms relative to the simvastatin regimen without STS. Overall, this study offers an entry point for understanding and verifying the clinical applications of STS-statin integrative therapy in treating patients with CHD. 

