## 2. Methods/Design

### 2.1. Setting and Design

This trial is a monocentric, parallel-design, randomized, controlled, clinical pilot study that will be conducted at Xiyuan Hospital, and China Academy of Chinese Medical Sciences in Beijing, China. Subject recruitment is scheduled to begin in August 2012. This study will involve 72 patients with the diagnoses of CHD and BSS according to Western medicine and TCM, respectively. The 72 participants will be randomized 1 : 1 into a standard Western therapy (control) group and an East-West integrative therapy (experimental) group. For 14 days, all 72 patients will be treated with a standard Western therapy involving simvastatin, and patients in the experimental group will additionally receive intravenous STS. Data will be collected before initiating treatment, immediately after the 14-day treatment period and 30 days posttreatment. Serum CRP levels measured by high-sensitivity CRP (hsCRP) testing will serve as the primary outcome parameter, whereas the levels of other inflammatory markers, the improvement of angina and BSS symptoms, and safety will serve as secondary outcome parameters.

The study design is illustrated in Figure 1 and described in detail below according to the CONSORT 2010 statement [11].

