### 2.3. Subject Inclusion and Exclusion

To participate in this study, subjects must be 35 to 75 years of age and must either have a previous history of myocardial infarction or have at least one coronary artery stenosis ≥50% confirmed by coronary angiography. In addition, subjects must currently be hospitalized with either unstable angina or an acute non-ST segment elevation myocardial infarction and have taken statin medicine for at least 1 month. From a TCM perspective, study participants must have the diagnosis of BSS. Finally, subjects must have a serum hsCRP level between 3 mg/L and 15 mg/L.

The criteria for exclusion include infection, fever, trauma, burn injury, or surgery within one month prior to recruitment; a concomitant diagnosis of cancer, sexually transmitted diseases, tuberculosis, or rheumatoid arthritis or other autoimmune diseases; or a history of serious pulmonary, hepatic, renal, neurological, psychiatric, or hematological diseases. In addition, subjects must not have previously undergone or currently be planning to undergo surgical intervention for CHD. Patients with severe heart failure indicated by an ejection fraction <35% will be excluded as will those with a reduced platelet count or a tendency to bleed or hemorrhage. Study participants must not currently be taking antibiotics or using TCM preparations that relieve fever or clear internal heat. Finally, patients who may become noncompliant or may participate in other clinical trials will be excluded.

During the course of the study, a subject may be excluded if (1) it is discovered that a subject was misdiagnosed for either BSS or CHD or was otherwise inappropriately accepted for participation in the trial; (2) if a subject misses a significant number of treatments or is missing significant records of data; (3) if subject's blood samples from the first two phases of the study (see Section 2.9) are contaminated or damaged in any way such that reliable data cannot be obtained; or (4) if for any reason (e.g., onset of a mid-study nosocomial infection), patient's inflammatory marker levels may not accurately reflect atherosclerotic inflammation. 

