### 2.9. Data Collection Phases

Table 1 indicates the data to be collected at each phase of the study. At Phase I, before treatment for the trial is initiated, each patient's full medical history will be recorded, along with vital signs, symptoms of present illness, and all current medications. Tongue and pulse examination will be performed by experienced TCM physicians. Laboratory tests will include routine blood, urine, and stool tests, an electrocardiogram, an hsCRP test, and various other tests measuring cardiac markers (creatine kinase, CK-MB; troponin T, cTnT; troponin I, cTnI), liver and kidney function, blood lipid and glucose, and coagulation. A 10 mL blood sample will also be collected from each patient, centrifuged, and stored at −80°C for subsequent measurement of other inflammatory mediators (IL-6, TNF*α*, VCAM-1, CD40, sCD40L, MCP-1, and MMP-9) at the end of the study. Finally, the severity of each patient's angina and BSS symptoms will be quantitatively scored.

Phase II marks the end of the 14-day treatment period, at which time the medications specific to this study (i.e., simvastatin and STS) will be discontinued and the patients reassessed. Again, vital signs, symptoms of present illness, tongue and pulse exam results, and all current medications will be recorded. Angina and BSS scoring will be repeated, along with all Phase I laboratory tests aside from those measuring cardiac markers and blood lipid and glucose. As in Phase I, a blood sample from each patient will be collected and preserved for subsequent analysis of secondary inflammatory factors at the end of the study. A preliminary, nonstatistical evaluation of treatment safety and efficacy will also be performed by the data collectors.

Thirty days after simvastatin and STS are discontinued, Phase III data will be recorded, including level of hsCRP, angina and BSS scores, vital signs, symptoms of present illness, tongue and pulse exam results, and all current medications. As before, a blood sample for analysis of secondary inflammatory factors will be collected, and treatment safety and efficacy will again be preliminarily evaluated.

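### Section 2.9 stops simvastatin together with STS at Day 14 and names no statin for the 30 days to the Phase III hsCRP reading

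*Protocol article*

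**What the plan says.** Section 2.3 admits patients hospitalised with unstable angina or NSTEMI who "have taken statin medicine for at least 1 month". Section 1 describes the design as "Using standard Western therapy involving simvastatin as a foundation", and Section 2.1 says "For 14 days, all 72 patients will be treated with a standard Western therapy involving simvastatin".

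Section 2.7 fixes simvastatin at 20 mg each evening in both arms. It is given "in addition to any other oral or IV Western medications or TCM preparations (aside from those listed as exclusion criteria, above", with the further condition that the other drugs be judged suitable as standard treatment for that patient. On who decides, it says: "These other medications will be prescribed by physicians who are not associated with the trial". The treatment described there runs for 14 days.

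Section 2.9 says that at Phase II "the medications specific to this study (i.e., simvastatin and STS) will be discontinued and the patients reassessed". It times the last visit from that stop: "Thirty days after simvastatin and STS are discontinued, Phase III data will be recorded, including level of hsCRP". Section 2.6 promises of the participants, "none of whom will be denied a standard, accepted therapy".

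**The concern.** Section 2.9 gives an instruction, and repeats it as the reference point for Phase III: stop simvastatin at Day 14. The same document calls that drug part of standard therapy, and the patients are acute coronary inpatients who were on a statin before they entered. No section says that they return to their earlier statin, continue simvastatin outside the trial, or take none.

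Two things are at stake.

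- **Safety.** Staff who follow Section 2.9 to the letter withdraw a statin two weeks after trial treatment starts in patients admitted with unstable angina or NSTEMI. Section 1 itself credits statins with fewer ischaemic cardiac events.
- **Interpretation of Phase III.** Section 1 also says that statins lower CRP, and hsCRP is the primary outcome parameter. A reading taken 30 days after both drugs stop, with statin use left open, does not show what happens when STS alone is withdrawn.

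**Working it through.** The plan gives no figure on this point to reproduce. The check compares sections and counts days.

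**Days covered by a statin rule**
- Simvastatin is specified from Day 0 to Day 14 (Sections 2.1, 2.7).
- Phase III falls 30 days after the stop (Section 2.9): 14 + 30 = Day 44.
- Share with a statin specified: 14/44 = 31.8%.
- Share with none specified: 30/44 = 68.2%, in both arms and so for all 72 planned patients.

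**What the Day 14 stop means depends on what happened to the entry statin**
- If simvastatin took the place of the entry statin, as the foundation wording in Sections 1 and 2.1 suggests, Section 2.9 stops the only statin that the protocol names. Section 2.6 is then honoured only if someone starts another, and no section says so.
- If the entry statin continued alongside simvastatin, stopping simvastatin leaves the patient on a statin, and Sections 2.6 and 2.9 agree.
- The text does not choose. The drugs barred in Section 2.3 are antibiotics and certain fever-relieving or heat-clearing TCM preparations. No statin rule appears there or in Section 2.7.

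**Phase II hsCRP**
Up to Day 14 both arms receive simvastatin under one rule. Section 2.9 places the stop and the reassessment at the same time point, so no off-simvastatin period precedes the Phase II sample. The stop cannot disturb that comparison.

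**Phase III hsCRP**
Between Day 14 and Day 44 two things can change: STS ends in the experimental arm, and simvastatin ends in both arms with an unstated successor. The text handles the arms alike, so it builds in no between-arm difference. However, the statin background against which STS withdrawal is observed is undefined and may vary from patient to patient. Section 2.9 and Table 1 record current medications at all three phases. That would show what was taken, but it sets no rule.

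**The case against.** The strongest reply is that nothing conflicts. A drug can be standard care and also be fixed by protocol for a set period; Sections 2.1, 2.7 and 2.9 all agree on 14 days. On this view Section 2.9 ends what the trial supplies, usual care by the non-trial physicians resumes, and Section 2.6 guarantees it. No section requires a statin-free month. Post-trial medication is also a detail that a journal article may leave to the full protocol.

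Much of this stands. The two descriptions of simvastatin are not in themselves contradictory, and physicians would probably restart or continue a statin. What remains is that Section 2.9 is an explicit order to stop, not a silence, and that reconciling it with Section 2.6 requires the reader to supply a sentence the document does not contain.

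Three stronger readings are tempting and are not supported:

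- **That patients take two statins during Days 0 to 14.** Section 2.7 limits other drugs to those suited to standard treatment, which makes a second statin unlikely. The missing rule on the entry statin is omitted detail only.
- **That the arm comparison is biased.** Handling is the same in both arms. Physicians may know the allocation, so later statin choices could differ by arm, but nothing in the document indicates that they will. For scale only, assume 30 completers per arm, a net k = 1 to 4 more patients on another statin in one arm, and a log hsCRP shift d of 0.1 to 0.3. The between-arm ratio then moves by exp(kd/30) − 1, from exp(0.1/30) − 1 = 0.3% to exp(1.2/30) − 1 = 4.1%. These inputs are assumptions, and the result does not measure the problem raised here.
- **That Phase III is uninterpretable.** It remains a randomised comparison of 14 days with and without STS, followed to Day 44. It cannot be read as the effect of withdrawing STS on continued statin therapy.

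**Conclusion.** The point holds in a limited form. Section 2.9 orders simvastatin stopped at Day 14 in patients admitted with unstable angina or NSTEMI, all on a statin at entry, and no section names a successor. That fits poorly with Section 2.6, and it leaves the statin background undefined for the 30 days before the Phase III hsCRP reading, 68% of the time from Day 0.

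The safety part assumes that simvastatin replaced the entry statin, which is the likelier reading but is not stated, and that staff apply Section 2.9 literally. The Phase III part needs neither assumption, because statin status is unspecified under either reading. The Phase II contrast is untouched. No effect size on hsCRP can be derived from the document. Priority is minor, on grounds of safety wording and Phase III interpretation.

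**What to change.** In Section 2.9, state that only STS is stopped at Phase II and that statin therapy, either simvastatin 20 mg or another statin chosen by the treating physician, continues in both arms to Phase III. Time Phase III from the end of STS. Report statin use at Phase III by arm, as a descriptive table from the current medications already recorded.

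This brings Section 2.9 into line with Section 2.6 and lets Phase III be read as STS withdrawal on continued statin therapy. It needs no new visit or data and no change to eligibility or randomisation.

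There are two costs. Phase III is no longer an off-simvastatin reading, although the protocol states no purpose for one. The 10 volunteers reported by February 2013 may also have been handled under the current wording; their recorded medications would show this.

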## 1. Background

Cardiovascular disease is the worldwide leading cause of death. Globally in 2008, over 17 million people died from cardiovascular diseases, representing 30% of total deaths around the world [1]. Among all cardiovascular diseases, coronary heart disease (CHD) is responsible for the greatest mortality, accounting for 7.3 million deaths worldwide in 2008 [1]. 

CHD involves narrowing of the arteries supplying oxygen to the heart, most often due to buildup of atherosclerotic plaque in the coronary vessels. The ultimate rupture of atherosclerotic plaque may lead to the onset of acute coronary syndrome (ACS), a medically emergent manifestation of CHD involving unstable angina or myocardial infarction. 

The formation of atherosclerotic plaque is an inflammatory response, usually associated with elevated levels of low-density lipoprotein cholesterol (LDL-C) in the blood [2]. To this end, statins have served as a notably successful pharmacologic intervention against CHD from the standpoint of Western medicine. One meta-analysis study found that the average statin regimen reduces LDL-C levels by 35%, leading to a 60% decrease in ischemic cardiac events such as those of ACS [3]. Remarkably, as demonstrated by the PRINCE study, statins also moderate the atherosclerotic inflammatory response by reducing levels of C-reactive protein (CRP) [4], a robust marker of systemic inflammation whose concentration in the blood strongly correlates with the patient's cardiovascular risk [5]. Nevertheless, a multicenter study involving over 4,000 ACS patients showed that 22.4% of patients receiving intensive statin therapy suffered a serious cardiovascular or cerebrovascular event within two years of initiating treatment [6], indicating that although statins may be one of Western medicine's most effective agents for CHD, the toll of this disease remains significantly high.

At East-West integrative medical centers in Asia, cardiovascular diseases may also be evaluated according to the principles of Traditional Chinese Medicine (TCM). Among patients with the Western diagnosis of CHD, the TCM diagnosis of blood stasis syndrome (BSS) is exceedingly common, and the treatment for these CHD-BSS patients via TCM frequently involves herbal therapies using the root of *Salvia miltiorrhiza* (*丹参*, danshen) [7].

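### Section 2.7 permits danshen and other tanshinone IIA products in both arms during the 14 treatment days, which could dilute the hsCRP contrast

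*Protocol article*

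**What the plan says.** Protocol article, section 2.7: controls receive 20 mg simvastatin each evening, "in addition to any other oral or IV Western medications or TCM preparations (aside from those listed as exclusion criteria, above"). The experimental arm has the same background: "In addition to receiving the treatments described above for the control group", each patient receives 80 mg STS intravenously every day. On who chooses the background drugs: "These other medications will be prescribed by physicians who are not associated with the trial".

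The exception in section 2.7 points back to section 2.3, where the only rule on medicines by class is: "Study participants must not currently be taking antibiotics or using TCM preparations that relieve fever or clear internal heat". Section 2.3 also requires every participant to have blood stasis syndrome (BSS).

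The Background (section 1) says that "the treatment for these CHD-BSS patients via TCM frequently involves herbal therapies using the root of" *Salvia miltiorrhiza* (danshen), that "The danshen root contains tanshinone IIA, an active biochemical compound", and that a notable property is "the ability of tanshinone IIA to decrease the levels of numerous inflammatory mediators associated with the progression of atherosclerosis, such as CRP". Serum hsCRP is the primary outcome (section 2.8).

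Current medications are recorded at Phases I, II and III (section 2.9 and Table 1).

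**The concern.** The trial asks what STS adds to a simvastatin-based regimen. STS is a formulation of tanshinone IIA, and danshen contains tanshinone IIA. By the protocol's own account danshen is a common TCM treatment for patients with this pair of diagnoses, yet the background-medication rule leaves it open in both arms. The sponsor restricted TCM that acts on fever and heat but not TCM containing the compound under test.

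This is a stated rule with a closed exception, so it is more than a detail left to a fuller document. A fuller document could repair it only by departing from the text printed here.

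A control patient who takes such a product during the 14 days may have a lower hsCRP at Phase II for the same reason as a patient in the STS arm. Blinded laboratory work does not undo that, because the exposure itself differs from what the comparison assumes. The bias would be towards no difference. A null result could then not be read as showing that STS adds nothing, in a trial whose Discussion already concedes that power may be insufficient.

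**Working it through.** **Step 1: is the product permitted?** Section 2.7 allows any TCM preparation except those in the section 2.3 list. That list names antibiotics and fever-relieving or heat-clearing TCM. The Background ties danshen to treatment of blood stasis, and nothing in the document classes it as heat-clearing. Danshen and tanshinone IIA products are named nowhere as prohibited, so they are permitted.

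**Step 2: is STS itself permitted in controls?** Section 2.1 gives intravenous STS additionally to the experimental group, section 2.5 lets the random number decide which therapy a patient receives, and section 2.9 describes STS as specific to the study. The intent is that controls do not receive it. No sentence says so to the outside prescribers.

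**Step 3: when does use bias the contrast?** Let *c* and *e* be the shares of control and STS patients exposed, *f* the product effect as a fraction of the STS effect, and *a* the fraction of it that adds on top of STS. With a true standardised effect *d*:

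 d_eff = d × (1 − c·f + e·f·a)

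The contrast is intact when c = e and a = 1. It shrinks when c exceeds e·a.

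**Step 4: how large could it be?** The plan states no power, effect size or SD, so there is no figure of its own to reproduce here.

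- From the document: 30 completers per arm (section 2.4, the group size taken from the comparable trial) and two-sided 0.05 (section 2.11).
- Assumed: *c*, *e*, *f*, *a*, and an SD of 1 throughout. The anchor is d = 0.736, the effect that gives 80% power.
- Method: two-sample t-test, noncentral t, 58 degrees of freedom, noncentrality d_eff × √(30/2).

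Example: c = 0.3, f = 1, and e = 0 or a = 0 give d_eff = 0.736 × 0.7 = 0.515 and power 50%.

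| Scenario (all assumed) | d_eff | Power |
|---|---|---|
| Equal use, fully additive | 0.736 | 80% |
| No matching gain in STS arm, f = 1, c = 10% | 0.662 | 71% |
| same, c = 20% | 0.588 | 61% |
| same, c = 30% | 0.515 | 50% |
| No matching gain in STS arm, f = 0.5, c = 10% | 0.699 | 76% |
| same, c = 30% | 0.625 | 66% |
| c = e = 30%, a = 0.5, f = 1 | 0.625 | 66% |
| c = e = 30%, a = 0.5, f = 0.5 | 0.680 | 74% |
| c = 30%, e = 20%, a = 1, f = 1 | 0.662 | 71% |

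The pattern does not depend on the anchor. With c = 30%, f = 1 and no matching gain, power falls from 48% to 27% at d = 0.5 and from 97% to 76% at d = 1.0.

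If 20% of 36 are lost, 28.8 per arm remain, so 30 is slightly generous.

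**The case against.** **STS as background care.** A reader might infer that section 2.7 lets controls receive STS on the same footing as any other product. The document does not support that. Sections 2.1, 2.5 and 2.9 treat STS as the allocated drug. What stands is only that no text expressly bars an outside physician from prescribing it.

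**The comparator wording.** A reader might also take "relative to the simvastatin regimen without STS" as the definition of the hsCRP comparison and conclude that danshen use breaches it. That phrase belongs to the aim on safety and on angina and BSS symptoms. The inflammation aim, one sentence earlier, is to add STS to standard therapy built on simvastatin. A control taking oral danshen is still not taking STS, and the document does not compare the tanshinone content of any danshen product with 80 mg of intravenous STS.

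**Balance.** Both arms have the same background rule, prescribers are outside the trial, and randomisation tends to balance existing use. This is a fair point. The document does not say whether prescribers know the arm, so heavier use in controls cannot be asserted. Balance alone protects the contrast only if the product's effect adds in full on top of STS, which is not known.

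**Pilot and ethics.** The trial is a pilot on individualised care, and section 2.6 promises that nobody is denied standard therapy. A total ban would sit badly with that, so the remedy needs a clinical-need exception.

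**Recording.** Current medications are recorded at all three phases, so much of the use can be described. Recording does not prevent use, and a product started and stopped between two visits is current at neither.

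**Conclusion.** The point holds for danshen and other tanshinone IIA products: the text permits them in both arms, and the protocol itself says that danshen is frequent in this kind of patient and that its compound lowers the primary outcome. For STS itself it is a gap in wording, not in intent.

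The size is unknown. The Background's remark on frequency concerns patients treated with TCM and gives no share for these inpatients. The range runs from no loss to a fall from 80% to 50% when 30% of controls are exposed at full STS-equivalent effect with no matching gain in the STS arm. Half-effect cases at 10% to 30% control exposure lie between 66% and 76%. These figures illustrate sensitivity and do not forecast the trial's power. A reader might infer that the trial is already compromised, but the document contains no exposure data to support that.

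The change is worth making because it is cheap and, with 10 volunteers reported by February 2013 (Trial Status), most of the planned 72 patients were still to come.

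**What to change.** Add to section 2.7, for both arms from randomisation to the Phase II blood draw: *No STS other than the study infusion, and no new start of any other preparation containing danshen or tanshinone IIA, oral or IV, unless there is a documented clinical need with no suitable alternative.*

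Also state that:

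- patients already on such a product at enrolment keep product and dose unchanged in either arm;
- patients who start one stay in their randomised arm and are not removed under the mid-study exclusions of section 2.3;
- the existing medication record is extended to product, dose and days of use between visits, and use is reported by arm, including recorded use in patients already randomised.

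**Cost.** Outside prescribers accept a small restriction for 14 days, and the case report form gains a few fields. No eligible patient is turned away, so recruitment is not slowed. Dilution from existing users remains, but it can be described.

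**Alternative.** Excluding existing users would remove that residual dilution at a price in recruitment. If all 10 volunteers over 3 to 4 months were enrolled, the rate is 2.5 to 3.3 per month, and the remaining 62 take about 19 to 25 months (62/3.33 and 62/2.5). If 20% of eligible patients were lost (an assumption), this becomes about 23 to 31 months (18.6/0.8 and 24.8/0.8). That trade-off is debatable and is not needed for the main repair.
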